### Data collection and management

#### Data collection methods

For this study, each household will be provided with a specific identification (ID) number. The child included in the study from each household will receive a unique personal, three-digit ID number (village number/household number/person number). All forms and datasets will identify participants by their unique identifier numbers, and names will not be used. The geographic coordinates of all study households will be documented at the beginning of the study and used in mapping the study points. Questionnaires and forms used will be initially prepared in English and translated into Amharic for data collection and then it will be translated back to English later. The questionnaire has already been validated. We will use the questionnaire for collection of the malaria KAP, socio-economic, socio-demographic, the acceptance of HS, challenges related to HS utilization, LLINs ownership and utilization. There are questions pertaining to PPT acceptance, utilization, and other opinion. Databases will be password protected and accessible only to authorized personnel. All documents will be securely stored in locked filing cabinets and accessible only to authorized personnel.

### Community sensitization and communication

Awareness creation on the purpose of the study, on the type of the interventions, and the need to involve in the study will be communicated to the community members through existing channels such as local government centres and through health extension workers. Farmers will be randomly selected to be part of the trial, and this could create some confusion among community members and lead into unnecessary misinformation. In this regard, the randomization process will be clarified to the community members to clear the misinformation and further explain that the community members at the receiving end of the intervention do not have any role whatsoever in the process of selection.

### Epidemiological data collection methods

A rapid diagnostic test (RDT), Microscopy and dry blood spot (DBS) will be used to measure the epidemiological parameters. In addition, prevalence of anaemia and splenomegaly among the study participants (children) will be graded according to their Hb level and by observation respectively. The axillary temperature will be taken fortnightly by health extension workers from all enrolled study children and if the child shows ≥37.5 °C or history of fever in the past 48 h, then, a rapid diagnostic test (RDT, CareStart® Malaria Pf/Pv combo test; Access Bio, Inc., Somerset, NJ, USA) will be conducted to further cross check the presence of malaria parasite. In line with this, blood spot sample (DBS) will be collected for later testing using PCR-based methods. In this regard we propose to collect two set of malaria case data. The first one is monthly epidemiological data that is collected based on clinical symptoms during the house-to-house visit and the second set of epidemiological data is obtained through active annual malaria prevalence survey. Monthly case follows up and testing of febrile cases will be conducted using malaria RDT kit whereas the annual active parasite screening will be done using diagnostic tools, Microscopy and DBS. The combination of diagnostics will be used to fill the gap among the tools. For instance, asymptomatic and sub-microscopic cases will be detected using the DBS PCR approach. The monthly house to house follows up will be made by health extension workers. The annual prevalence survey will be made by licensed laboratory technicians and health extension workers. In all instances, malaria positive children will be provided with a full dose of *Artemether-lumefantrine* (AL) and chloroquine by a trained health worker following national guidelines. In Ethiopia, CHWs are trained and mandated to test and treat malaria.

### Entomological data collection methods

A total of 10 houses, (five houses for indoor and five houses for outdoor LTs) catches will be selected from each study village. Indoor and outdoor catches will be collected from each study arm. Mosquitoes will be collected indoor and outdoor from 6:00 pm to 06:00 am from each selected house using standard battery-operated CDC light traps. Traps will be hung from the ceiling or from roof support at the foot end of the bed where people sleep at night and each trap will be suspended about 1.5 m from the floor. Traps will be also hung outdoor under the eaves of the house for outdoor mosquito collection. Each trap will be set by trained research team members. Collection bags will be retrieved from traps in each house in the morning between 06:00 am and 07:00 am. All unfed, fed, half gravid and gravid adult female *Anopheles* mosquitoes (Indoor and Outdoor) will be identified using taxonomic keys of Gilles and Coetzee (1987) [42]. Dried head and thorax of *Anopheles gambiae* s.l., and *Anopheles pharoensis* collected by CDC light traps from each study villages *(Kebeles)* will be carefully separated from the abdomen and tested for *P. falciparum* and, *P. vivax-210 and P. vivax-247* circumsporozoite proteins (CSPs) simultaneously following the protocol developed by Beier et al. 1988 [43]. On agricultural pest assessment, the severity of infestation will be scored on visual observation of the foliar damage attributed to each pest using a 1 to 5 scale, where 1 is clean with no visual infestation symptoms, 2 = very little damage, 3 = high level of damage where plants show the presence of FAW larvae feeding and most of the young leaves show infestation symptom, 4 = severe damage where almost 75% of the leaves are severely affected and excrement is visible on the infested areas and the maize whorls, and 5 = very severe damage where total plant damage due to FAW is visible.

### Socio-economic data collection methods

Semi-structured questionnaire will be prepared to collect socio-demographic data at the beginning and end of the study. Each study household will be observed for durability of the screening material, the presence of holes, tears, losses and the fitness of windows and doors. The presence or absence of LLINs and the number and age of people who slept under bed nets in the previous night will be assessed in every visit to mosquito sampling (before and after screening). The impact of screening intervention on bed net use rate will be measured by observing bed net use among household members before and after house screening intervention, and between intervention and control groups. For the social science component of this impact evaluation, the team will collect data using household surveys, focus group discussions and key informant interviews. A baseline survey, midline survey and end line surveys will be undertaken using a structured household survey questionnaire and trained enumerators.

### Study endpoints/outcomes

#### Clinical evaluations

The main outcomes of the clinical study will be the malaria incidence, splenomegaly, and anaemia. Thus, the baseline clinical survey of all study children will take place between Sept and Oct 2020 to determine the clinical parameters. As part of the follow up, starting from Nov 2020, trained health extension workers will visit the house of each child and take data of clinical symptoms, temperature, and splenomegaly (sign of spleen enlargement). While monthly follow up of the child continues throughout the 2 years of study period (Sept 2020 to Dec 2022) for documentation of any malaria incidence, blood testing of the entire cohort of the study children will be repeated at the end of each rainy season (Sept/Oct 2021) and Sept/Oct 2022). In between the annual clinical surveys (i.e., at the time of monthly follow up), blood testing will be done only to children who develop fever to minimize community fatigue development. Temperature measurement, RDT testing, blood haemoglobin measurement, blood sample collection for microscopy will be conducted by a licensed laboratory professional following the WHO guideline [44].

### Entomological evaluations (medical entomology)

The major entomological outcomes of the study are changes in mosquito densities, rates of mosquito infection (sporozoite rates), and the entomological inoculation rate (EIR). Both indoor and outdoor mosquito collections will be made using the Centres for Disease Control (CDC) light traps to estimate the mosquito density. Collections will be made twice per year (July to Sept and January to March) starting from July 2020 to Oct 2022. All mosquito collections will be preserved in silica gel and transported to the International Centre of Insect Physiology and Ecology (ICIPE) Kenya, Nairobi, ICIPE molecular laboratory, where they will be identified to species level and examined for sporozoite infection using Polymerase chain reaction (PCR) technique. Blood meal analysis of fed females will be done using Enzyme linked immunosorbent assays (ELISA).

### Entomological evaluations (agricultural entomology)

In line with the investigation of vectors of medical entomology, the agronomics team will evaluate the efficacy of PPT against stem borers, fall armyworm (FAW) and striga infestation. Visual observation will be made in selected plots from each treatment arm (PPT plot and control) and the degree of infestation will be measured using scale scores where 1 attributes to clean plant with no infestation and 5 attributes to very severely damaged plant [45].

### Economic and social science evaluations

The actual outcomes for the economic and social evaluations are discussed in detail in Abro et al. 2020. “Social networks, incentives, and diffusion of house screening and push-pull technology interventions in rural Ethiopia.” AEA RCT Registry. April 06. 10.1257/rct.5642-1.0. The primary outcomes are PPT knowledge score, PPT and HS adoption productivity of maize (kg/ha), milk productivity (kg/animal), cost of illness (USD/household), malaria prevalence (%), lost working days due to malaria, and lost school days due to malaria for children. We have also other secondary outcomes such as willingness to pay for PPT and HS, women and children dietary diversity score, and household food insecurity access scale (HFIAS) [46].

### Data management and access

Data will be stored in two forms, i.e., hard, and soft copies in compliance with the principles of good clinical practice protecting the confidentiality of participants. Specimens of mosquitoes, blood film slides and genotype print of PCR outcomes will be maintained by the principal investigator and be available up on request from authorized representatives, regulatory bodies. The results of the study will be made publicly available through peer reviewed journals.

### Statistical methods

#### Malaria incidence data analysis

Change in clinical malaria incidence over 2 years period among the treatment and control arms will be determined using Poisson distribution. In this trial we will follow modified ITT protocol and if a child is lost from follow up, or withdraw from the study, or refuse to be included in the treatment, it will be immediately replaced by a child from the reserve list. The Relative Risk (RR) and RR Reductions (RRR) will be calculated with corresponding 95% confidence intervals to compare dichotomous variables, and difference in means will be used for additional analysis of continuous variables. Mixed effects Poisson model will be used to test the difference in incidence rates among the study arms, to determine effects of the repeated measurements within house, village, the effect of year and village-intervention interaction effects. To control the effect of clustering or village and individual level confounding factors such as gender and age, these covariates will be fitted in to random effects during analysis. If a child is diagnosed with malaria case within 28 days of the first episode with the same plasmodium species, then it will be put on treatment as part of the safety protocol, however, the case will not be included in the analysis. The prevalence of anaemia among the study participants (children) will be analysed using the guideline developed by world health organization [47]. Accordingly, all children between 6 and 59 months of age, whose Hb level is recorded between 10.0–10.9 g/dl, 8.0–9.9 g/dl and less than 8.0 g/dl will be graded as mild, moderate, and severe, respectively. In line with this we will also report community level anaemia prevalence. Thus, a prevalence of anaemia will be stated as severe if it is documented over 40% (combining mild, moderate, and severe) and moderate if the prevalence is 20–39.9%. Both malaria and anaemia prevalence data will be compared in the intervention and control houses using multilevel mixed-effects logistic regression models, taking village effects into account.

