##### Recruitment

For this study, the principal investigator (AA) will be based in the study district and form a recruitment committee. The committee will be composed of the head of local administration, representative from village HEWs, the head of local health center and the principal investigator (AA). The team will make house-to-house visits and explain the objective of the study to the candidate household heads. The list of candidate households will be separately generated from the roster containing the list of household heads of the district by the data manager (ZA). In instances where the candidate household refuses to participate, reserve candidate households will be invited to participate.

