**Fig. 1 Fig1:**
[figure not shown]
Flow chart of the study

In this study, a total of 167, 246, 250 and 175 houses will be included in four different treatments, treatment 1 (control, LLINs only), treatment 2 (LLINs and HS), treatment 3 (LLINs, HS and PPT) and treatment 4 (LLINs and PPT), respectively. The differences in sample size across arms is due to differences in number of households within each sub-village. To full fill the total sample size, we did the random selection based on population size of each sub-village. Census of children under 14, and above 14 years of age will be made in all 838 households selected. One child will be randomly selected from each house for annual malaria parasite survey. In addition to the annual parasite screening survey, monthly follow up will be implemented in all households to monitor clinical malaria by health extension workers. If a child moves or quits the study, we will replace the child from the same house. In instances where the whole family leaves the area, we will document them as lost to follow up.

The selected children will be checked up every month for clinical symptoms of malaria infection, splenomegaly, and development of anaemia. Blood test will be conducted if the child develops clinical symptoms. The child will also be surveyed at the beginning and end of each transmission season to estimate the prevalence of *Plasmodium species* infection, parasite density, and the prevalence of anaemia. Collections will be made from both indoor and outdoor settings.

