#### Handling of dropouts/withdrawals

The right of participants to withdraw from the study at any time without giving a reason will be communicated prior to recruiting each participant. If the first child from the house is moved to other place for various reasons, the second child will be replaced. In unlikely scenario of the situation in which the entire family moves (e.g., building home in nearby town is a common practice in the area), the follow up will be discontinued and other related data collection activities (entomology and social science) will be replaced by reserve house.

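### The modified intention-to-treat rule replaces children who are lost, withdraw or refuse treatment from a reserve list, so the children analysed may no longer be comparable between arms

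*Protocol article*

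**What the plan says.** The rule is in the Protocol article under Statistical methods, Malaria incidence data analysis: "In this trial we will follow modified ITT protocol and if a child is lost from follow up, or withdraw from the study", and it continues "or refuse to be included in the treatment, it will be immediately replaced by a child from the reserve list". Loss, withdrawal and refusal of treatment therefore have the same consequence.

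Three other sections deal with replacement:

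- **Study flow chart (text under Fig. 1).** "If a child moves or quits the study, we will replace the child from the same house". For a departing family: "In instances where the whole family leaves the area, we will document them as lost to follow up".
- **Handling of dropouts/withdrawals.** "If the first child from the house is moved to other place for various reasons, the second child will be replaced", which I read as the second child taking the first child's place. If the whole family moves, "the follow up will be discontinued and other related data collection activities (entomology and social science) will be replaced by reserve house".
- **Recruitment.** "In instances where the candidate household refuses to participate, reserve candidate households will be invited to participate".

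The Blinding section says that screening cannot be concealed, while blood-film readers are blinded. The Sequence generation and Randomization sections give the sub-kebele as the unit of allocation. No section says that a replaced child stays in the analysis in the assigned arm.

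**The concern.** Intention to treat compares groups as they were allocated, whether or not the intervention was taken up. Here, refusing the treatment is itself a reason to swap the child for another. The control arm has no screening and no PPT to refuse, whereas each of the other three arms has one or both. PPT also asks for training and plot preparation. If refusal is more common in the intervention arms, they fill up with children from accepting households, while control keeps both kinds. Any link between willingness to accept and malaria risk then enters the rate ratio.

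Replacements are made with the arm visible. Blinded microscopy does not help, because the problem is who is analysed and not how a slide is read. The first child is chosen at random within the house, but nothing says that the substitute is. A substitute also brings a different age and malaria history into a house that the mixed Poisson model treats as a repeated unit.

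At stake is the comparison of clinical malaria incidence between arms. If refusers are replaced and not followed, their outcomes cannot be recovered later.

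**Working it through.** **1. Who can be affected.** From the Study flow chart section, the arms are 167 (control), 246, 250 and 175, and 167 + 246 + 250 + 175 = 838. Households offered HS, PPT or both number 246 + 250 + 175 = 671. If 10-15% of these were replaced for refusal, that would be 0.10 × 671 = 67 to 0.15 × 671 = 101 children. The 10-15% is an assumption, as the protocol gives no refusal rate.

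**2. Size of the distortion when there is no true effect.** The plan has no figure of its own to reproduce, so this is an illustration. Let *r* be the share of refuser-type children and *h* their incidence relative to acceptors. Both are assumed. Suppose refusers stay in control but are fully replaced by acceptors in the intervention arm, and contribute no person-time there. With acceptor incidence set to 1:

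- control rate = (1 − r) + r·h
- intervention rate = 1
- apparent rate ratio = 1 / [(1 − r) + r·h]

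| r | h | Denominator | Apparent rate ratio |
|---|---|---|---|
| 0.10 | 1.5 | 0.90 + 0.15 = 1.05 | 0.95 |
| 0.15 | 1.5 | 0.85 + 0.225 = 1.075 | 0.93 |
| 0.10 | 2 | 0.90 + 0.20 = 1.10 | 0.91 |
| 0.15 | 2 | 0.85 + 0.30 = 1.15 | 0.87 |
| 0.10 | 0.5 | 0.90 + 0.05 = 0.95 | 1.05 |
| 0.15 | 0.5 | 0.85 + 0.075 = 0.925 | 1.08 |

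Milder and more extreme assumptions widen the range: r = 0.05 with h = 1.5 gives 1/1.025 = 0.98, and r = 0.30 with h = 3 gives 1/1.60 = 0.63.

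**3. What removes it.** If h = 1, the ratio is 1. If control refusers of the same type are replaced to the same extent, both rates are 1 and the ratio is again 1. If half of them are replaced (r = 0.10, h = 2, so 5% remain in control), the ratio is 1/(0.95 + 0.10) = 0.95 instead of 0.91.

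**4. The replacement rules side by side.**

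| Event | Malaria incidence data analysis | Study flow chart | Handling of dropouts/withdrawals |
|---|---|---|---|
| Child moves or quits | Child from reserve list | Child from same house | Second child of the house (covers moving only) |
| Whole family leaves | Child lost, so reserve list | Lost to follow-up, no replacement child named | Follow-up ends; only entomology and social data go to a reserve house |
| Refuses treatment | Child from reserve list | Not covered | Not covered |

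The last two columns agree with each other, and the first conflicts with both. Because eligibility requires only one child per household, the same-house rule cannot always be applied. It also cannot repair a household's refusal of screening or PPT, since a sibling lives in the same house.

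**The case against.** The strongest reply has four parts.

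- **Refusal may not differ by arm.** The article often uses the word treatment for study arm, control included. Refusing treatment could mean declining to take part, and every arm faces home visits and blood tests. This stands in part: control children can also refuse, so the assumption of no replacement in control is an extreme. It does not make refusal equal, because control has no HS or PPT to decline.
- **The allocation survives.** Under sub-kebele randomisation, a replacement from the same house or cluster leaves the cluster in its arm. This stands. A reader might infer that the randomisation itself is broken. The documents do not support that; what is weakened is the comparability of the children analysed.
- **Observed person-time may be kept.** The text says that the child is replaced, not that earlier data are deleted, and an analysis plan may settle the matter. This stands for lost or withdrawn children and would reduce the bias. It helps little for a child who refuses at the outset and is never followed.
- **The other sections are narrower.** They are, but neither covers refusal of treatment, so they do not soften the rule.

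Three further inferences are tempting but not supported:

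- That the bias must favour HS and PPT. Nothing says that refusers have higher incidence, and the sign reverses if theirs is lower.
- That the flow chart and dropout sections disagree on a departing family. Both end the child's follow-up.
- That a reserve house would enter malaria follow-up late and unscreened. Under the dropout section, reserve houses supply only entomology and social data, and nowhere is it said where reserve-list children live.

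**Conclusion.** The point holds as a defect in a stated rule, not as a gap left to an analysis plan. Replacing treatment refusers after allocation is not intention to treat, whatever the label, and refusal and replacement can differ by arm in an unblinded trial where HS and PPT are offered only to some. The direction of the bias is unknown and its size cannot be derived from the document. Under assumed one-sided replacement of 10-15% and no true effect, the apparent rate ratio lies between 0.87 and 1.08, depending on whether refusers have up to twice or only half the incidence of acceptors. Those figures also assume that replaced refusers contribute no person-time. The conflict between the reserve-list rule and the same-house rule is established from the text and needs no assumption.

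**What to change.** - **Primary analysis.** Include every originally selected child in the assigned arm, with observed person-time as the Poisson offset, censored at loss or withdrawal.
- **Treatment refusers.** Keep them in their arm and follow them wherever consent to follow-up continues. Refusing screening or PPT should not end outcome follow-up.
- **Replacement children.** Use them only in a sensitivity analysis.
- **One rule.** State the same replacement source and triggers in Study flow chart, Malaria incidence data analysis and Handling of dropouts/withdrawals, covering refusal and departure of the whole family. Drop the modified intention-to-treat label, or define it to match.
- **Reporting.** Give refusals and replacements by arm and reason, including reserve households drawn at recruitment.

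The cost is wording, follow-up of refusers, and the loss of replacement children's person-time from the primary analysis. Counting person-time from same-house replacements alongside that of the originally selected children is a possible alternative. It recovers some precision, but brings children chosen after allocation into the main comparison, so I would keep it as a sensitivity analysis.

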**Methods:**

A four-armed household, cluster-randomized, controlled study will be conducted to assess the combined impact of HS, LLINs and push-pull agricultural technology (PPT) against clinical malaria in children in Ethiopia. The unit of randomization will be the household, which includes a house and its occupants. A total of 838 households will be enrolled in this study. In this trial 246 households will receive LLINs and HS, 250 will receive LLINs, HS and PPT, 175 households will receive LLINs and PPT. The remaining 167 houses which receive LLINs only will be used as control. One child aged ≤14 years will be enrolled per household in each treatment and followed for clinical malaria using active case detection to estimate malaria incidence for two malaria transmission seasons.

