#### Study flow chart

The study design is summarized in a flow chart as shown in Fig. 1. The study contains four treatments randomly assigned to households with village as the blocking factor. As some houses get screening and others not, there could be a risk of diverting potentially infectious mosquitoes from screened houses to unscreened ones. Thus, to avoid such risks care will be taken to not exceed 5% of houses per village as it was recommended from previous studies from The Gambia [14]. Studies conducted in other countries confirmed that the risk of mosquito spread to unprotected houses is unlikely to increase if the proportion of houses protected is less than 10% [5, 14].

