### Sequence generation

As described in the Section of study population all the households in the district are eligible to the treatment. The unit of randomization is the sub-village (*sub-kebele*) level. For this study, we divided the 30 villages *(Kebeles)* into 66 sub-villages/sub-kebeles. In each sub-kebele, we will obtain a fresh list of farmers, which are organized into one-to-five groups.^1^ Each *sub-kebele* will be randomly assigned into the four treatment arms.

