### Randomization

As the study area is composed of different localities (and elevations) of the district, the risk of malaria infection also varies among *kebeles* (document review from district malaria information). Therefore, the study area will be first clustered into *kebeles* and then each kebele will be clustered in to *sub-kebeles*. The randomization process will be conducted using the STATA’s *sampsi* package and using *sub-kebele* as a unit of randomization. Efforts will be made to ensure that each *kebele* receives balanced number of treatments following the standard protocol developed by Pinder et al. (2016) [14]. Stratified randomization by *sub-kebeles* will take out the kebele effect and the likelihood of chance imbalances between study arms. All entomological, epidemiological, and social studies will be conducted following the same rule described above i.e., stratified randomization. The randomization will be done by ZA to prevent selection bias by concealing the allocation sequence from the field researchers assigning sub-kebeles into the four treatment arms until the moment of assignment. Thus, both the chief investigator and the principal investigator will not be involved in the randomization process.

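### The protocol contradicts itself on whether households or sub-kebeles are randomised, and the stated models do not clearly carry the sub-kebele into the analysis

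*Protocol article*

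**What the plan says.** **Unit of randomisation.** The protocol article gives two answers.

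- Abstract, Methods: "The unit of randomization will be the household, which includes a house and its occupants".
- Study flow chart: "The study contains four treatments randomly assigned to households with village as the blocking factor".
- Sequence generation: "The unit of randomization is the sub-village". The 30 kebeles are divided into 66 sub-kebeles, and each sub-kebele "will be randomly assigned into the four treatment arms".
- Randomization: the person who randomises works by "concealing the allocation sequence from the field researchers assigning sub-kebeles into the four treatment arms until the moment of assignment". The same section says that stratification "will take out the kebele effect and the likelihood of chance imbalances between study arms".

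**Analysis.** Under Malaria incidence data analysis, a mixed-effects Poisson model is to be used "to determine effects of the repeated measurements within house, village, the effect of year and village-intervention interaction effects". Clustering by village and the individual confounders gender and age are then taken together: "these covariates will be fitted in to random effects during analysis". Malaria and anaemia prevalence are to be compared with mixed-effects logistic models in which village is the only level named. Elsewhere the article uses village to mean kebele, and Sequence generation separates it from the sub-village or sub-kebele. No model names the sub-kebele.

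**The concern.** The two descriptions are different designs. If households were allocated individually within villages, a village effect would be an adequate account of the design. If whole sub-kebeles are allocated, every child in a sub-kebele is in the same arm. Any difference in malaria risk between sub-kebeles of one kebele then enters the comparison of arms. A model with only a kebele intercept does not put that variation into the standard error. A house intercept does not help either, because it describes repeated visits to one child and not what neighbouring houses share.

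At stake are the error rates for malaria incidence and anaemia, both listed as main clinical outcomes, and for malaria prevalence. The Randomization section itself says that malaria risk differs between kebeles and links this to locality and elevation, so zero variation between sub-kebeles would be hard to assume.

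**Working it through.** **Inputs from the protocol article.** Arms of 167, 246, 250 and 175 households (Study flow chart); 167 + 246 + 250 + 175 = 838, as stated. 66 sub-kebeles in 30 kebeles and four arms (Sequence generation). Significance level 5% (Sample size rationale). The article gives no ICC, design effect or cluster-adjusted error rate, so there is no figure of its own to reproduce on this point. The ICC values below are assumptions.

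**Step 1: which design fits the rest of the text.** The flow-chart text explains the unequal arms by differences in sub-village size. That fits allocation of sub-kebeles, as does the description of concealment.

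**Step 2: cluster size.** 838/66 = 12.7 households per sub-kebele; 66/30 = 2.2 sub-kebeles per kebele.

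**Step 3: error rate if the sub-kebele is left out.** Design effect DE = 1 + (12.7 − 1) × ICC; true alpha = 2 × [1 − Φ(1.96/√DE)]. For ICC 0.05, DE = 1 + 11.7 × 0.05 = 1.58 and true alpha is 12.0%.

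**Step 4: check by simulation under no effect.** 30 kebeles, 66 sub-kebeles and 838 households were simulated, comparing LLINs plus screening with control. There were 1,500 runs per setting, with an assumed kebele ICC of 0.05. A linear mixed model stood in for the Poisson and logistic models, so the percentages are approximate (Monte Carlo standard error about 0.6 points near 5%). Where two figures appear, the first is for arms balanced within kebeles and the second for unrestricted allocation.

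| Sub-kebele ICC (assumed) | DE | Formula alpha | Village intercept only | Village + random village-by-arm | Village + sub-kebele |
|---|---|---|---|---|---|
| 0.01 | 1.12 | 6.4% | 6.7 / 5.7% | 5.2 / 4.8% | 5.2 / 4.8% |
| 0.02 | 1.23 | 7.8% | 7.2 / 6.9% | 5.1 / 5.2% | 5.1 / 5.3% |
| 0.05 | 1.58 | 12.0% | 12.5 / 10.1% | 6.5 / 5.8% | 6.5 / 5.3% |
| 0.10 | 2.17 | 18.3% | 18.9 / 17.4% | 6.5 / 5.4% | 6.5 / 5.3% |

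At a sub-kebele ICC of 0 (balanced allocation only) the three models gave 5.2%, 4.3% and 4.3%.

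**Step 5: why the interaction matters.** If the sub-kebeles of a kebele receive different arms, each village-by-arm cell is exactly one sub-kebele. A random village-by-arm term is then the same as a sub-kebele intercept. Under unrestricted allocation there are on average 56 cells for 66 sub-kebeles, so it is nearly the same. A fixed interaction works differently. There are 30 × 4 = 120 possible cells and at most 66 can be filled, so at least 54 are empty. The sub-kebele differences are absorbed into the fixed cell means and do not reach the standard error, and the main arm effect has no clear meaning.

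**Step 6: the stratification claim.** Let x kebeles hold all four arms and each of the others hold at least one sub-kebele. Then 4x + (30 − x) ≤ 66, so 3x ≤ 36 and x ≤ 12. At least 18 kebeles must lack one or more arms. With an even split (24 × 2 + 6 × 3 = 66), no kebele holds all four.

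**The case against.** A reader might infer that all the planned p-values are too small. The document does not support that for incidence. The incidence model is a mixed model that lists a village-by-intervention effect, and Step 5 shows that this term, if random, does almost the same work as a sub-kebele intercept. The text does not say that it is random, and it stands beside the year effect among the effects to be determined, so a fixed reading is equally open. The objection therefore stands against a flat claim about incidence, but it leaves an ambiguity that decides whether the test is valid. It does not reach the prevalence and anaemia models, where only village is named.

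Two other strong readings also fail. Households are not treated as fully independent, because village effects are in every model; the gap is within the kebele. Placing age and gender among the random effects does not by itself shrink the p-value for arm.

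It can also be said that an analysis plan, not shown here, may set out the full random-effects structure. That would excuse silence. But the article does state the levels of its models, and these do not match its own allocation. On stratification, the article promises only efforts towards balance within kebeles, and village effects are already to be fitted. What is too strong is the statement that the kebele effect is removed.

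**Conclusion.** The contradiction over the unit of randomisation is plain and must be reconciled. If sub-kebeles are the unit, the prevalence and anaemia tests as written are anti-conservative whenever the sub-kebele ICC is above 0: about 6% to 18% in place of 5% for an assumed ICC of 0.01 to 0.10. The size depends wholly on that unknown ICC. For incidence the conclusion is conditional. With a random village-by-intervention term the simulated error rate was 4.3% to 6.5%; with a fixed term or none, the sub-kebele variation stays out of the standard error. Fitting the confounders age and gender as random effects is a separate specification error, and the claim about the kebele effect is a separate overstatement.

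**What to change.** 1. Reconcile the abstract and the flow-chart text with Sequence generation and Randomization. If the last two describe the design, state the sub-kebele as the unit of randomisation throughout.
2. In the incidence, malaria prevalence and anaemia models, include a random intercept for sub-kebele, with kebele as the stratum and child or house for repeated measurements. For incidence, an explicitly random village-by-intervention term would serve in place of the sub-kebele intercept. It should not be a fixed term in the model that gives the main arm effect.
3. Fit arm, year, age and gender as fixed effects.
4. Replace the claim that stratification takes out the kebele effect by a statement that allocation aims at balance within kebeles and that the analysis adjusts for kebele.

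These are changes of wording that need no new data. The cost is somewhat wider confidence intervals where sub-kebeles do differ.
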